### 2.14. Bias Control

Selection bias will be controlled by applying the same selection criteria to the participants in the different groups to be compared, which will have identical monitoring. In addition, in the collection of information, a record of losses to follow-up will be kept, collecting as much information as possible about them. Regarding misclassification bias, smoking will be considered as a criterion of truth, the measurement of 6 or more ppm of CO in exhaled air by CO-oximetry. Finally, multivariate analysis using logistic regression will control for various confounding factors.

### 2.15. Security Event Reporting

As this is a NON-PHARMACOLOGICAL intervention study, adverse events related to the drug used as inclusion criteria will be reported according to standard practice protocol through the Spontaneous Reporting of Adverse Reactions Programme of the Andalusian Centre for Pharmacovigilance.

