### 2.9. Study Variables

The data collected will correspond to the following study variables, both outcome and explanatory.

Outcome variables will be: number of cigarettes smoked daily (discrete quantitative) *; smoking cessation (dichotomous): variable calculated on the basis of whether the number of cigarettes is equal to 0, and exhaled air CO-oximetry detects a value equal to or less than 10 ppm *; blood pressure (continuous quantitative); heart rate (continuous quantitative); weight in kilograms (continuous quantitative) *; and Body Mass Index (BMI) (continuous quantitative): variable calculated on the basis of weight and height) *.

Explanatory variables are sex (qualitative polychotomous); age (discrete quantitative); occupation (qualitative); postcode of residence (qualitative); cumulative smoking (discrete quantitative) *; and physical nicotine dependence measured by the Fagerström test [19] (discrete quantitative); psychological dependence, as measured by Glover Nilsson’s test [20] (discrete quantitative); motivation to quit smoking, as measured by the Richmond test [21] (discrete quantitative); weekly alcohol consumption (Standard Drinking Units-UBE) (discrete quantitative) *; World Health Organisation (WHO) Global Physical Activity Questionnaire (GPAQ) [22] and Benisovich’s physical activity self-efficacy scale [23].

(*) Some of the outcome variables can be considered intermediate variables of other explanatory variables, due to their causal relationship.

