### 2.11. Intervention

Interventions will be developed by a multidisciplinary team with experience in tackling tobacco consumption. Physical exercise recommendations will be made by specialists in Medicine, Physical Education, and Sport Sciences and will be carried out in line with the Andalusian Physical Exercise Prescription Plan (APEPP) [1], the recently published regional plan for Andalusia. Therefore, this study consists of two treatment arms:A.Smokers who are going to be prescribed targeted physical exercise and brief advice to stop smoking while receiving cytisinicline treatment (1.5 mg tablets) according to the care process: EXPERIMENTAL ARM.B.Smokers who will receive a standard leaflet explaining physical exercise to the general population and brief advice on smoking cessation when starting cytisinicline treatment, according to the care process: CONTROL ARM.

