### 2.12. Participant Chronology and Schedule of Visits

All participating smokers will be followed up, either in person or by telephone, according to the plan established in this study and at the visits indicated below (Figure 1):-Selection visit (Day 0): FACE-TO-FACE. The potential participant is proposed to participate in the study. A check is made to ensure that the patient has no medical or other history that might contraindicate the prescription of physical exercise. The patient receives the information and signs the informed consent form if he/she wishes to be included in the study.-Visit 0 (Day 0): FACE-TO-FACE. Baseline data are collected on the previously mentioned variables. The necessary criteria for prescription are completed. The drug is prescribed to be approved within 24h, and a treatment start date is set.-Visit 1 (Day 7 ± 2): TELEPHONE. Data are collected, and the participant is asked if there are any problems with the motivation to continue.-Visit 2 (Day 30 ± 4): FACE-TO-FACE. Data are collected, and questions are asked if there have been any problems with the physical exercise, motivating for its continuation.-Visit 3 (Day 60 ± 7): FACE-TO-FACE. Data are collected, and questions are asked if there have been any problems with the physical exercise, motivating for its continuation.-Visit 4 (Day 90 ± 7): FACE-TO-FACE. Data are collected, and a question is asked as to whether there have been any problems with the physical exercise, motivating the patient to continue.-Visit 5 (Day 180 ± 15): FACE-TO-FACE. Data are collected, and a question is asked as to whether there have been any problems with the physical exercise, motivating the patient to continue.-Visit 6 (Day 365 ± 30): FACE-TO-FACE. Data are collected.

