Visit 3 (Day 60 ± 7)	High-Level 3.1	Cardiorespiratory Endurance	High-intensity intervals (HIIT)	5–6	Vigorous (~75–90% max HR)	45
	High-Level 3.2	Muscle Strength and Endurance	Squats (4 × 12), push-ups (4 × 12), lunges (4 × 12), heel raises (4 × 12), plank with lift (4 × 15 s), dumbbell rows (4 × 12)	3–4	Bodyweight exercise or Vigorous (~70–85% 1RM)	50
	High-Level 3.3	Flexibility or Range of Motion	Advanced stretches	2–3	Moderate	15
	High-Level 3.4	Neuromotor Capabilities	Advanced coordination exercises (agility ladder)	2–3	Vigorous	
Visit 4 (Day 90 ± 7)	High-Level 4.1	Cardiorespiratory Endurance	HIIT (vigorous intensity intervals)	5–6	Vigorous (~75–90% max HR)	50
	High-Level 4.2	Muscle Strength and Endurance	Squats (4 × 12), advanced push-ups (4 × 12), lunges (4 × 12), heel raises (4 × 12), plank with lift (4 × 12 s), dumbbell rows (4 × 12)	3–4	Bodyweight exercise or vigorous (~70–85% 1RM)	55
	High-Level 4.3	Flexibility or Range of Motion	Dynamic stretches	2–3	Moderate	15
	High-Level 4.4	Neuromotor Capabilities	Advanced balance exercises with unstable platform	2–3	Vigorous	
Visit 5 (Day 180 ± 15)	High-Level 5.1	Cardiorespiratory Endurance	HIIT with combined strength work	5–6	Vigorous (~75–90% max HR)	55
	High-Level 5.2	Muscle Strength and Endurance	Squats (4 × 12), advanced push-ups (4 × 12), lunges (4 × 12), heel raises (4 × 12), plank (4 × 15 s), dumbbell rows (4 × 12)	3–4	Bodyweight exercise or vigorous (~70–85% 1RM)	60
	High-Level 5.3	Flexibility or Range of Motion	Deep stretches	2–3	Moderate	15
	High-Level 5.4	Neuromotor Capabilities	Advanced dynamic balance exercises	2–3	Vigorous	

1RM: one repetition maximum; HR: heart rate.

**Table 4 healthcare-12-02516-t004:** Sequence of taking cytisinicline.

Days of Treatment	Recommended Dosage (1.5 mg)	Maximum Daily Dose
From the 1st to the 3rd day	1 tablet every 2 h	6 tablets
From the 4th to the 12th day	1 tablet every 2.5 h	5 tablets
From the 13th to the 16th day	1 tablet every 3 h	4 tablets
From the 17th to the 20th day	1 tablet every 5 h	3 tablets
From the 21st to the 25th day	1–2 tablets per day	2 tablets

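### The protocol plans no estimate by arm of harm from exercise, the randomised component: the only reporting route is for drug reactions, and no adverse event is among the data to be collected

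*Protocol article*

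**What the plan says.** Section 2.15 starts from the premise that the study is non-pharmacological. It then says that "adverse events related to the drug used as inclusion criteria will be reported according to standard practice protocol". The channel it names is the regional pharmacovigilance centre's scheme for spontaneous reports. It mentions no other kind of event.

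Section 2.11 describes the experimental arm as "Smokers who are going to be prescribed targeted physical exercise and brief advice to stop smoking while receiving cytisinicline treatment". The control arm also receives cytisinicline and brief advice, with a general leaflet on exercise. The prescribed exercise is therefore what differs between arms.

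Section 2.9 opens by tying the data collected to the variables it lists. The outcome list begins "Outcome variables will be: number of cigarettes smoked daily" and goes on to cessation, blood pressure, heart rate, weight and BMI. Neither the outcome list nor the explanatory list contains an adverse event or an injury.

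Section 2.12 states that "All participating smokers will be followed up, either in person or by telephone, according to the plan established in this study". At Visits 2 and 3 data are collected and "questions are asked if there have been any problems with the physical exercise, motivating for its continuation"; Visits 4 and 5 have equivalent wording. Visit 1 asks about motivation, and Visit 6 mentions data collection only.

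**The concern.** The reasoning in section 2.15 is the wrong way round for this trial. That the tested intervention is not a drug is a reason to leave drug reactions to routine channels. It is also a reason to set up trial-level recording of harms from the exercise. The section does the former only, and so provides for the background treatment common to both arms and not for the randomised component.

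Spontaneous pharmacovigilance reports carry no trial denominator and no split by arm. If the plan is followed as written, the trial may conclude that prescribed exercise is a useful adjunct to cessation treatment with no planned count of injuries or cardiovascular events beside that conclusion. Events that are not asked about in the same way at the time are hard to recover reliably afterwards.

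**Working it through.** The article states no safety rate, event count or safety power, so there is no planned figure to reproduce. The check has two parts.

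**1. Is an exercise-related event captured anywhere, by arm?**

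- Section 2.15: a route for drug reactions; exercise events are not mentioned.
- Section 2.9: no adverse event or injury variable.
- Section 2.11.1: foresees injury or discomfort and provides a substitute exercise. The exercise itself is recorded in the electronic notebook and in DIRAYA. No event is defined or recorded as an outcome.
- Section 2.4.2: recognises risk of adverse events as a ground for exclusion, so the possibility of harm is acknowledged.
- Section 2.12: asks about exercise problems at days 30, 60, 90 and 180, with no definition, grading or named variable.
- Section 2.13: regression models are named for cessation and number of cigarettes. No safety summary is named.

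The visit question also has a gap in time. The last stated enquiry is at Visit 5 (day 180) and follow-up ends at Visit 6 (day 365). That leaves 365 − 180 = 185 days, or 185/365 = 51% of follow-up, with no scheduled enquiry. The strength sessions prescribed at Visit 5 are the longest in each of Tables 1 to 3 (35, 45 and 60 minutes).

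**2. What would a count by arm show at the planned size?**

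Input: n = 75 per arm (section 2.3). All event rates below are assumptions.

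*Upper limit with zero events*, two-sided exact 95%: 1 − 0.025^(1/n).

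- n = 75: 1 − 0.025^(1/75) = 4.8%
- n = 60 (an assumed 15 lost): 1 − 0.025^(1/60) = 6.0%

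*Chance of at least one event in the exercise arm*: 1 − (1 − p)^n.

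| True rate p | n = 75 | n = 60 |
|---|---|---|
| 1% | 52.9% | 45.3% |
| 2% | 78.0% | 70.2% |
| 5% | 97.9% | 95.4% |

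*Power to compare arms*, two-sided 5%, normal approximation, with p̄ the mean of p1 and p2: Φ{(|p2 − p1| − 1.96·√[2p̄(1 − p̄)/n]) / √[(p1(1 − p1) + p2(1 − p2))/n]}.

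- 2% vs 5%: (0.0300 − 1.96 × 0.0300)/0.0299 = −0.96, power 17%
- 5% vs 15%: (0.1000 − 1.96 × 0.0490)/0.0483 = 0.08, power 53%
- 5% vs 20%: (0.1500 − 1.96 × 0.0540)/0.0526 = 0.84, power 80%

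The approximation is rough at such small counts, but the message is clear: 75 per arm can describe and bound a risk, and can detect only large differences.

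**The case against.** The strongest reply is that section 2.15 says where drug reactions go and does not say that other events go unrecorded. The article condenses a fuller protocol, which may hold event definitions, grading, form fields and safety tables, and their absence here is no fault. The article is also not silent on exercise problems. It asks about them at four visits, applies that schedule to all participants, promises identical monitoring in section 2.14, foresees injury, and provides expert supervision and follow-up calls.

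Much of this stands. A reader might infer that exercise harms will never be counted by arm, that the trial cannot state the risk, or that a signal would be assembled nowhere. The article does not support those readings. The answers at Visits 2 to 5 may well be written down and could be tallied later.

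Nor should one picture all participants doing vigorous intervals on 5–6 days a week. That describes Table 3 only. The starting level is set by the GPAQ result, Table 1 stays at low to moderate intensity, and section 2.4.2 excludes several cardiovascular conditions.

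Nor would a table by arm settle benefit against risk. The power figures show that it would be descriptive, which suits a study that calls itself a pilot.

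What the reply does not remove is the content of the sections themselves. Section 2.15 addresses harm and names a route for the shared drug alone. Section 2.9 sets out what data will be collected and includes no harm. The visit question is joined to encouragement to continue, is linked to no variable, and leaves the second half of follow-up uncovered. It refers to the physical exercise, so answers from a leaflet-only control arm would not be comparable even under identical monitoring.

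**Conclusion.** The point holds in this form: the article gives a reporting route only for reactions to a drug that both arms take, lists no adverse event or injury among the data to be collected, and does not link its exercise-problem question to a defined variable or a summary by arm. As written, no estimate of exercise harm by arm is planned. This is more than missing detail, because the sections that fix safety reporting and data collection both leave out the randomised component.

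The loss is moderate. Complete recording in 75 participants would support an upper limit of 4.8% if no event occurred, and a higher limit with losses to follow-up. It would give a 78% chance of seeing at least one event at an assumed true rate of 2%. It would not give a useful test between arms unless the difference were large. These figures assume full follow-up of the exercise arm, and the event rates are illustrative.

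**What to change.** - Add adverse events to section 2.9: musculoskeletal injury, cardiovascular event and any serious event.
- Ask the same structured question in both arms at every existing visit, including Visit 1 and Visit 6, and record the answers in REDCap.
- Report number and percentage by arm with exact 95% confidence intervals, labelled as descriptive.
- Report events that stop the prescribed exercise for the experimental arm only, since the control arm has no prescription to stop.
- Extend section 2.15 to refer to this record, and keep the pharmacovigilance route for drug reactions.

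The cost is one form, a few minutes at visits that already take place, slightly more data entry, and a short amendment through the ethics committee under section 2.18. The change needs no new visits and alters no dose, exercise level or clinical rule.

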### 2.16. Ethical and Regulatory Framework

This study will be conducted in strict accordance with the ethical principles for research involving human participants, in accordance with the Declaration of Helsinki-Fortaleza, and with the legal regulations in force on research and personal data protection (Law 14/2007 on Biomedical Research and Organic Law 3/2018 on Personal Data Protection and guarantee of digital rights), Regulation (EU) 2016/679 of the European Parliament and of the Council, of 27 April 2016 on the protection of natural persons with regard to the processing of personal data and on the free movement of such data and repealing Directive 95/46/EC (General Data Protection Regulation), Organic Law 3/2018 of 5 December on the Protection of Personal Data and the guarantee of digital rights, and Law 14/2007 of 3 July on Biomedical Research.

This study is committed to respecting the rights of participants, including their dignity, autonomy (Law 41/2002, basic law regulating patient autonomy and rights and obligations regarding clinical information and documentation) and well-being, and to conducting the research in a way that maximises the potential benefits to society while keeping risks and discomfort to participants to a minimum.

### 2.17. Ethics Committee

Before starting the study, the protocol was reviewed and approved by the Cordoba Research Ethics Committee by resolution of 30 July 2024 with code SICEIA-2024-001451.

### 2.18. Amendments to the Protocol

Any amendment to be made by the research team must be submitted to and obtain prior authorisation from the competent ethics committee for each amendment, which, failing this, will be the Cordoba Research Ethics Committee.

### 2.19. Informed Consent

All participants will be informed of the objectives, procedures, potential benefits and risks associated with the study, as well as their right to withdraw from the study at any time without any consequences for their medical care. Written informed consent will be obtained from each participant prior to inclusion in the study.

### 2.20. Confidentiality and Data Access Policy

The confidentiality of participants’ personal data will be guaranteed at all times, and such data will be processed in accordance with the applicable regulations on personal data protection, ensuring their anonymity and the security of their storage and processing. Only the research team will have access to identifiable data.

### 2.22. Performance Advertising Policy

Any disclosure of results shall be made in such a way that it is not possible to identify any participant.

The results of this study, whatever they may be, will be published in indexed scientific journals and subsequently disseminated through digital media (social networks, websites) to reach the general population.

### 2.23. Gender Perspective

A gender perspective in research is a necessary approach to properly understand and address the differences and inequalities that exist between men and women in relation to tobacco use. The inclusion of this perspective not only enriches the analysis of data but also improves the effectiveness of health interventions and policies aimed at reducing smoking and its consequences.

Numerous studies have shown that there are significant differences in smoking patterns between men and women. Historically, men have had higher rates of tobacco use than women. However, the gap has been narrowing in recent decades in many regions of the world [27]. In addition, the motivations and circumstances that lead individuals to initiate and maintain tobacco use can vary considerably by gender. For example, women may be more influenced by factors related to stress and body image, while men may be more influenced by social and cultural factors [28,29]. In this sense, our study contemplates a descriptive analysis of the data for each group, including gender as a qualitative explanatory variable. In addition, we address a common barrier to smoking among women smokers, namely weight gain after smoking cessation.

The impact of tobacco use on health also shows gender differences. Female smokers have a higher risk of developing cardiovascular disease compared to male smokers and also face unique risks, such as complications during pregnancy and negative effects on reproductive health. Furthermore, certain types of tobacco-related cancers, such as lung cancer, may manifest differently in men and women, underscoring the need for specific approaches to prevention, diagnosis and treatment [30,31].

Tobacco control interventions and policies may have different effectiveness according to gender. Smoking cessation programmes that do not consider gender differences may be less effective for one group or the other. For example, women may respond better to interventions that address weight and stress management, while men may benefit more from approaches that emphasise the economic and social impact of smoking. Thus, a gender perspective allows for the design of more tailored and effective interventions [32]. In this regard, our study considers two different smoking cessation interventions, both of which have an impact on aspects such as weight gain (physical exercise) or economic impact (NHS-funded medication).

Gender inequalities may also influence access to and adherence to the resources needed to quit smoking. Women may face additional barriers, such as lower income, caregiving responsibilities and social stigma, which make it difficult for them to access smoking cessation programmes [33]. As mentioned above, one way to address these barriers is the use of a drug that is currently funded by the NHS, which facilitates access for people with fewer financial resources. On the other hand, the prescription of targeted physical exercise is intended to ensure a close follow-up of patients, which would encourage adherence to these programmes among this group of smokers. Integrating a gender perspective in this type of research contributes to a more inclusive science and the promotion of public health in an equitable manner.

### 2.24. Registration in Clinical Trials

The study is registered in clinical trials under the code NCT06579846 and can be consulted at the following link:

https://clinicaltrials.gov/study/NCT06579846?viewType=Card&sort=StudyFirstPostDate&limit=50&term=cytisinicline&intr=Exercise&rank=1 (accessed on 10 December 2024).

In this respect, the research protocol complies with the SPIRIT (Standard Protocol Items: Recommendations for Interventional Trials) guidelines for the design and reporting of clinical trials.

## 3. Expected Results

The primary results will allow us to estimate the efficacy of prescribing physical exercise as an adjuvant therapy to classic multicomponent treatment, incorporating it as an additional element to be considered when it is accepted by the smoker. Secondly, we will find out, in young smokers, its acceptance as an optional therapy, with the high cost-effectiveness of quitting smoking as early as possible in the life of smokers.

We will also learn about the influence of the prescription of physical exercise in the female gender in relation to barriers such as weight gain and/or obesity, generally associated with smoking cessation. In addition to the potential added benefit in the control of associated dependent variables such as arterial hypertension, hyperglycaemia and dyslipidaemia, which are directly related to “physical inactivity” as an independent variable that is becoming increasingly relevant in our digital society.

The results obtained would be immediate, in terms of improving the smoker’s health, from the moment the smoking cessation process begins in synergy with the prescription of controlled physical exercise. We believe, therefore, that the results will affect the improvement in the level of health of smokers who achieve abstinence from smoking by improving their quality of life and, in the long term, their average life expectancy through the control of at least two risk factors such as smoking and physical inactivity. And not only to facilitate immediate smoking cessation but also to prevent craving and/or subsequent relapses, with a positive impact on the quality of life of people who achieve smoking cessation.

With regard to the improvement in public health, we understand that the results will favour the reduction of the prevalence of active smoking. Also, passive smoking in those people who involuntarily breathe in smoke from cigarette combustion when living with smokers in the study population. Moreover, reducing smoking has a positive impact on environmental health, in line with the Sustainable Development Goals (SDGs) and the 2030 Agenda of the UN General Assembly. In this sense, the results could be framed along the lines of “health and well-being”, “climate action” (as it implies improving the environment by reducing waste in the form of cigarette butts and environmental tobacco smoke), dangers such as fires from incandescent cigarette butts, and “reducing inequalities” since the most vulnerable people smoke, and more intensively.

